## Abstract

**Background:**

Persistent symptoms, described as long COVID or post-COVID-19 condition, pose a potential public health problem. Here, the design and recruitment of the PRIME post-COVID study is described. PRIME post-COVID is a large-scale population-based observational study that aims to improve understanding of the occurrence, risk factors, social, physical, mental, emotional, and socioeconomic impact of post-COVID-19 condition.

**Methods:**

An observational open cohort study was set up, with retrospective and prospective assessments on various health-conditions and health-factors (medical, demographic, social, and behavioral) based on a public health COVID-19 test and by self-report (using online questionnaires in Dutch language). Invited for participation were, as recorded in a public health registry, adults (18 years and older) who were tested for COVID-19 and had a valid Polymerase Chain Reaction (PCR) positive or negative test result, and email address. In November 2021, 61,655 individuals were invited by email to participate, these included all eligible adults who tested PCR positive between 1 June 2020 and 1 November 2021, and a sample of adults who tested negative (2:1), comparable in distribution of age, sex, municipality of residence and year-quarter of testing. New recruitment periods are planned as well. Participants are followed over time by regular follow-up measurements. Data are analyzed using the appropriate data-analyses methods.

**Discussion:**

The PRIME post-COVID study will provide insights into various health-related aspects of post-COVID-19 condition in the context of various stages of the COVID-19 pandemic. Results will inform practical guidance for society, clinical and public health practice for the prevention and care for long-term impact of COVID-19.

**Trial registration ClinicalTrials.gov identifier:**

NCT05128695.

## 1. Introduction

Since 2020, the severe acute respiratory syndrome coronavirus-2 (SARS-CoV-2), causing coronavirus disease 2019 (COVID-19), has been disruptive to societies, globally. By August 2022, over 596 million confirmed cases were counted, accompanied by ~6 million deaths worldwide (1). An acute infection can be diagnosed using Polymerase Chain Reaction (PCR) testing and often presents with symptoms such as fever, cough, tiredness, and loss of taste or smell (2). The majority of the infections progress with mild symptoms and only few (up to a maximum of 20% in elderly) infected individuals require hospitalization (3, 4). Overall, men, people with more comorbidities, older age, and higher body mass index more frequently suffer a severe course of infection, resulting in a higher risk of hospitalization and dying as a consequence of COVID-19 (5, 6).

After great efforts to cope with new waves of SARS-CoV-2 infections globally, the Omicron wave had initially pointed to some hope of ending the pandemic (7), although situations may change quickly. Of an emerging concern are persistent symptoms after a SARS-CoV-2 infection (8–10). These persistent symptoms after COVID-19 are referred to as the patient-initiated term “long COVID” (11), “*a condition whereby affected individuals do not recover for several weeks or months following the onset of symptoms suggestive of COVID-19”* (12). As a global and standardized clinical case definition is lacking and various terminology is used to describe the same condition (13), the World Health Organization (WHO) released the term “post-COVID-19 condition” and a corresponding case definition. The WHO defined “post-COVID-19 condition” in October 2021 as “*a condition that occurs in individuals with a history of probable or confirmed SARS-CoV-2 infection, usually 3 months from the onset of COVID-19 with symptoms, that last for at least 2 months, and cannot be explained by an alternative diagnosis*” (14). Due to the high numbers of SARS-CoV-2 infections worldwide, post-COVID-19 condition poses a potential public health problem with a substantial impact on the socio-economic, emotional, and physical functioning of many individuals.

Currently, the impact of health problems after a SARS-CoV-2 infection are not fully understood, also the prevalence and incidence of post-COVID-19 condition are still unclear. Reasons for this unclarity include difficulties encountered in studying post-COVID-19 condition. In previous scientific studies, this translated into the inclusion of participants without a formal diagnosis of an acute infection, due to the lack of PCR test capacity in the first wave (15), and long-term symptoms after an acute infection (13), due to the lack of a globally accepted case definition at that time before the release of the recent WHO definition. Furthermore, study participants were followed at different time points since infection, participants represented a selected population instead of a population-based population, being included from hospital-based settings (16), medical records (17), peer support groups (9), or social media platforms (18). Furthermore, in many studies, a control or reference group of negatives was lacking (19). Including specific study populations may lead to selection bias and alongside with the lack of harmonization of measures, these limitations hamper the comparison between studies, for instance regarding prevalence, incidence, and impact on health or socioeconomics (20). Furthermore, established risk factors for post-COVID-19 condition are, for example, female sex and pre-existing co-morbidities (21–23), but there are still knowledge gaps on risk factor coherence and possible protecting factors (for example vaccination) for post-COVID-19 condition.

The current study, called Prevalence, Risk factors and Impact Evaluation of post-COVID-19 condition (PRIME post-COVID) study, was set up to gain more insight into the occurrence and impact of post-COVID-19 condition in the community, by including a large-scale population-based PCR positive sample, a negative control group, and follow-up measures for prospective assessment. The findings of this study will contribute to the development of holistic social and health care pathways and support systems. Here, the design and recruitment are described.

## 2. Methods and analysis

The aim of our study is to understand the prevalence, incidence, risk factors and impact of post-COVID-19 condition.

The following study questions will be addressed:

What is the prevalence and incidence of post-COVID-19 condition in PCR confirmed SARS-CoV-2 positive adults, by various definitions, accounting for occurrence of symptoms in negative tested adults?What are sociodemographic and medical risk factors (for example vaccination status and virus variant) for having, preserving, and recovering from post-COVID-19 condition?What is the impact of having post-COVID-19 condition on negative health outcomes and socioeconomic aspects, including social, labor, and educational participation?What is the role of having post-COVID-19 condition in maintaining positive health, including social, mental, emotional, and physical health?How can health be promoted in relation to post-COVID-19 condition, using tools from medical and other types of care, in recovery and coping with post-COVID-19 condition?

### 2.1 Design and setting

An observational cohort study in positive and negative COVID-19 PCR-tested adults, including a retrospective and prospective element, was conducted to reach the study aims (Figure 1). The design is an open cohort study, meaning that new participants will be included over time. The first inclusion was in November/December 2021.

**Figure 1 F1:**

Overview of the prospective and retrospective elements of the PRIME post-COVID study design.

The study region has ~500,000 adult inhabitants (24) in a mixed urban area. Until now, the South Limburg region presents a comparable number of COVID-19 cases per 100,000 inhabitants compared to the Dutch average (46,115 vs. 45,735, respectively), but the highest national mortality rate of 209 deaths per 100,000 inhabitants, compared to 128 deaths per 100,000 inhabitants nationally (not age-standardized) (25).

The Public Health Service (GGD) South Limburg is the main responsible organizer for regional COVID-19 testing in the study region. Testing was free of charge for all inhabitants in the region from 1 June 2020 onward. Tested persons are standardly registered in the Dutch COVID-19 database CoronIT. The study population was approached to participate from this registry.

The Strengthening the Reporting of Observational studies (STROBE) checklist was used in reporting this study (Supplementary Table 1).

### 2.2 Study population

The target population consisted of adults tested for COVID-19 at the GGD South Limburg with a valid PCR test result (positive/negative). We here describe the recruitment of people tested between 1 June 2020 and 1 November 2021. The GGD South Limburg tested 472,982 adults in this period. Eligible for participation were tested adults (18+ years) with a registered email address available. Of eligible adults, all people with a positive COVID-19 PCR test, and a sample of people with a negative COVID-19 PCR test were selected. All positives who met the inclusion criteria were invited to obtain a representative sample of all positives in the test registry. A reasonable sample of ~20,000 negatives were additionally included (ratio 2:1). Regarding the positives, when a person had tested positive multiple times, the record of the first positive COVID-19 test was used in the analyses, as we intended to include data on the first exposure. Regarding the negatives, a sample of people with a negative PCR test were randomly selected in each strata with a distribution that matched (1:2) positives; strata included combinations of age (18–20, 20–30, 30–40, 40–50, 50–60, 60–70, 70–80, and 80+ years), sex (man, woman), year-quarter of 2020 and 2021 in which PCR test was performed, and municipality of residence (*n* = 16) (Table 1). When tested negative multiple times, the information regarding the last negative COVID-19 test was used to have the greatest assurance that an invited control was not infected up to the point of inclusion. This procedure allowed to include a group of negatives, similar to the positives regarding sociodemographic and timing of testing.

**Table 1 T1:** Descriptives of invitees of the prevalence, risk factors and impact evaluation of post-COVID-19 condition (PRIME post-COVID) study.

**Test result, *n* (%)**	**Invitees** ***n*** = **61,655**	
	**Negative**	**Positive**
	19,875 (32.2)	41,780 (67.8)

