### 2.7 Statistical analysis

The obtained data will be analyzed using descriptive statistics, such as on prevalence of post-COVID-19 condition including 95% confidence intervals. To assess prevalence, participants tested negative are also presented, providing some insight of “background risk,” as symptoms of post-COVID-19 condition may be nonspecific and present in the general population (41, 42). Prevalence of reported symptoms in post-COVID-19 condition participants will be compared to the prevalence in PCR negatives. Post-COVID-19 incidence will be estimated when follow-up data is available, by determining the proportion of newly diagnosed participants (since baseline) meeting the post-COVID-19 condition criteria. Multivariable models are used to test for the likelihood of (long-term) symptoms in positive vs. negative participants, adjusted for possible confounders. Possible confounders include age, sex, underling disease, severity of COVID-19, and year-quarter when tested. Risk factor analyses, with post-COVID-19 condition as outcome, will be performed using multivariable logistic regression models. Various sensitivity analyses will be performed, e.g., by only including participants with highest certainty score 0. These are examples of analyses to answer a main study question. Appropriate statistical analyses will be performed to answer all study questions.

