### 3.1 Strengths and limitations

A major strength of this cohort study is the design comprising of a retrospective and prospective element. In general, including a large population-based sample is a strength, as large sample sizes promote precision and reliability of prevalence estimates and associations between post-COVID-19 condition and risk factors (43). By including a population-based sample we were able to minimize selection bias toward the inclusion of specific groups, such as hospital-based populations. Moreover, including PCR test-negative individuals to determine long-term symptoms and impact of the COVID-19 pandemic in general, made it possible to identify symptoms and impact accountable to a SARS-CoV-2 infection. Matching test-negatives to test-positives on key characteristics (i.e., sex, age, and year-quarter of testing) when sampling limits possible confounding by accounting for the distribution of these characteristics. Finally, a wide range of physical, emotional, social, and behavioral aspects will be mapped using extensive questionnaires, including multiple standardized and validated questions on diverse topics. Doing so enables us to approach post-COVID-19 condition holistically, and to correct future analysis for several confounding factors. By the comprehensive assessment in the current study, post-COVID-19 condition will be classified by several definitions put forward in the literature. These definitions will be compared with each other, and with the established case definition provided by the WHO as well.

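### Municipality was a sampling factor for the negatives but is not among the named confounders, the later lists of factors or Table 1, so the named model would not correct any residual imbalance on it

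*Protocol article*

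**What the plan says.** The protocol article describes the sampling of negatives in two places, and both include municipality. The abstract (Methods) calls the negatives "comparable in distribution of age, sex, municipality of residence and year-quarter of testing". Section 2.2 says they were "randomly selected in each strata with a distribution that matched (1:2) positives", and the strata combine eight age bands, sex, "year-quarter of 2020 and 2021 in which PCR test was performed, and municipality of residence", the last with 16 levels. That sentence then points to Table 1. The table as shown gives sex, age and year-quarter by test result, and nothing on municipality.

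Later sections give shorter lists.
- Section 2.7, on the model comparing symptoms in positives and negatives: "Possible confounders include age, sex, underling disease, severity of COVID-19, and year-quarter when tested".
- Section 3.1, on strengths: "Matching test-negatives to test-positives on key characteristics (i.e., sex, age, and year-quarter of testing) when sampling limits possible confounding".
- Section 3.1.1, on misclassification: the confounders said to be protected by registry linkage are again sex, age and year-quarter only. Section 2.3, however, includes municipality among the registry variables to be linked with consent.

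**The concern.** Three of the four factors that shaped the control sample are carried into the named adjustment set, and the fourth is not. If the match had succeeded, this would matter little, because matching on exposure would itself have balanced municipality between the invited groups. If it did not succeed, adjustment has to make up the difference. The plan names that repair for age, sex and year-quarter only.

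The contrast at stake is the one that separates symptoms attributable to infection from background symptoms: "Multivariable models are used to test for the likelihood of (long-term) symptoms in positive vs. negative participants, adjusted for possible confounders". Municipality can stand for socioeconomic mix and other local conditions, which may relate both to testing positive and to background symptoms. Because Table 1 omits it, a reader cannot tell whether the draw balanced it.

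**Working it through.** **Inputs.** All counts are from Table 1; the strata and the ratio are from section 2.2.

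**1. Reproducing the stated split.** 19,875 + 41,780 = 61,655. Negatives are 19,875 / 61,655 = 32.2% and positives 41,780 / 61,655 = 67.8%, as printed. The sex, age and year-quarter columns each sum to 19,875 and 41,780. Overall there are 41,780 / 19,875 = 2.10 positives per negative, close to the stated 2:1. An exact half of the positives would be 20,890, so the negatives are 1,015 (4.9%) short.

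**2. Was the match achieved on the factors that can be checked?** A 1:2 match within every cell would give 2.0 positives per negative in every row of Table 1. The distance below is half the sum of absolute differences in shares between the two groups; SMD is the multi-category standardised mean difference.

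| Factor | Lowest positives per negative | Highest positives per negative | Distance | SMD |
|---|---|---|---|---|
| Sex | 18,794 / 9,917 = 1.90 (men) | 22,986 / 9,958 = 2.31 (women) | 0.049 | 0.10 |
| Age | 2,252 / 1,525 = 1.48 (70–80) | 3,519 / 1,211 = 2.91 (18–20) | 0.071 | 0.20 |
| Year-quarter | 49 / 361 = 0.14 (2nd 2020) | 3,947 / 1,156 = 3.41 (4th 2021) | 0.114 | 0.46 |

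For June to September 2020 the shares are (361 + 2,267) / 19,875 = 13.2% of negatives and (49 + 716) / 41,780 = 1.8% of positives. Too few available negatives cannot explain that gap. Half of the 716 positives in the 3rd quarter of 2020 is 358, yet 2,267 negatives were invited.

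**3. What this implies for municipality.** Crossing the factors gives up to 8 × 2 × 7 × 16 = 1,792 cells, with a mean of 19,875 / 1,792 = 11.1 negatives and 41,780 / 1,792 = 23.3 positives per cell. Each cell belongs to one municipality, and the margins show that the 1:2 ratio failed in many cells. The design therefore does not guarantee balance on municipality. It does not show imbalance either: if the departures were spread evenly over municipalities, the municipality margin could still be balanced.

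**4. Size.** No municipality distribution is given, so the bias cannot be computed. As an illustration only, the shift in the crude difference is at most the distance between the groups on municipality times the range of symptom prevalence across municipalities. Assumed distances of 0 to 0.12 (the tabulated factors show 0.05 to 0.11) and assumed ranges of 5 to 20 points give:
- lowest: 0 × any range = 0 points;
- middle: 0.05 × 10 = 0.5 points;
- highest: 0.12 × 20 = 2.4 points.

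For scale, assume 10,000 positive and 4,000 negative respondents at 25% prevalence. The standard error of the difference is then √(0.25 × 0.75 / 10,000 + 0.25 × 0.75 / 4,000) = 0.0081, or about 0.8 points. These respondent numbers and the prevalence are also assumptions.

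**5. Cost of conditioning on it.** Sixteen levels need at most 15 fixed-effect terms.

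**The case against.** The strongest reply is that nothing has been excluded. The list in 2.7 is open: it says what the confounders include, and the section ends by calling its analyses examples. A journal article may leave the final covariate list to a full protocol or analysis plan. This stands, and it means municipality is not named rather than ruled out. The reply is weaker for sections 3.1 and 3.1.1, whose lists are worded as complete. Section 3.1.1 concerns misclassification rather than matching, but municipality is a linked registry variable and would belong there if it were regarded as a confounder.

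A second reply is that controls were selected by exposure, before the questionnaire outcome. Conditioning on the matching factors is then not required in principle, as it would be under case-control sampling; it matters only for residual imbalance on a factor that also predicts symptoms given the other covariates. This also stands. It does not dispose of the point, because the match failed on every factor that can be checked. Moreover, the analysis uses respondents rather than invitees, and section 3.1 itself expects that participation may differ by test result.

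A third reply is that a municipality main effect does not capture epidemic timing within a quarter, and that education, collected from everyone (Table 2), already covers part of the socioeconomic mix. Both are fair. They lower the expected gain but do not remove the reason to carry a design factor into the model.

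A reader might go further and infer that the groups are imbalanced on municipality and that the excess prevalence is biased as a result. The documents do not support that: they give no municipality distribution and no symptom prevalence by municipality, and poor balance on year-quarter does not establish poor balance on place.

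**Conclusion.** The inconsistency is real and minor. Municipality is a sampling factor in the abstract and in 2.2. It is not named in the adjustment set of 2.7, is missing from the lists in 3.1 and 3.1.1, and is not tabulated. Since the within-stratum match was not achieved on sex, age or year-quarter, matching alone cannot be relied on for municipality, and the model as named would not correct any residual imbalance.

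The size and direction of any effect are unknown, and zero is possible. The 0 to 2.4 point range rests wholly on assumed inputs and bounds a crude difference. A real bias would need both residual imbalance on municipality and a difference in symptoms between municipalities after adjustment for the named covariates. The article shows neither.

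**What to change.** 1. In section 2.7, add municipality of residence to the positive-versus-negative models, as a fixed effect or a random intercept. Take it from the registry for respondents who consented to linkage, and derive it from the postal code asked of all (Table 2) where linkage was refused.
2. Report the distribution of municipality by test result, in Table 1 or a supplement, so that balance can be judged.
3. Reconcile the lists in 2.7, 3.1 and 3.1.1 with the abstract and 2.2. If municipality is left out on purpose, give the reason.

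The cost is at most 15 model terms, against 61,655 invitees, plus one table block and small text edits. No new data are needed and no stated figure changes.

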### 2.3 Recruitment

Emails to invitees were send between 17 and 25 November 2021. Invited for participation were 41,780 PCR COVID-19 positives and 19,875 negatives from test records registered in the registry. Invitees received an email containing the invitation for participation, study information with a link to the website (containing the participant information and email address in case of questions), and a weblink to the online questionnaire.

Participants needed to be able to understand, read and write the Dutch language, as all materials were provided in Dutch.

Digital informed consent was asked before the questionnaire started. Further digital informed consent was asked to link data from the questionnaire to the registry data (age, sex, municipality, date of test, and test result).

A reminder was sent 1 and 3 weeks after the invitation to invitees who did not respond to the invitation or started but not completed the questionnaire. The questionnaire was made available using the MWM2 application of market research platform Crowdtech (ISO 27001 certified).

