The main limitation resides in the use of self-reported online questionnaire data. No additional clinical assessment or investigations on symptoms and physical fitness could be performed. This method of data collection (i.e., using self-administered questionnaires) is always susceptible to information bias. As expected with large-scale population-based studies, a number of the invitees might not respond. Invitees being less digitally skilled are hindered to participate without assistance, which might result in selection (non-response) bias and reduced external validity. The same holds for invitees who were unable to read or understand the Dutch language, as all materials were provided in Dutch. Differential selection bias might occur when the chance of participation is higher in test-positives vs. test-negatives, when positives believe to suffer from long-term symptoms since their infection. Possible over- and under representations of specific subgroups in the eventual study population will be considered when estimating post-COVID-19 condition prevalence, for example by weighing these subgroups according to the distribution in the invited population to enhance representativeness and thereby external validity. Overrepresentations may affect internal validity when non-participation of specified subgroups is related to both exposure and outcome. We will therefore study whether the association between risk factors and post-COVID-19 condition differs (i.e., heterogeneity of the effect) in different subgroups. Lastly, we acknowledge the possible limited generalizability of our results, due to the focus on the southern region of the Netherlands.

Despite these general strengths and limitations of the design, the retrospective and prospective elements both have their own strengths and limitations to be discussed.

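### The negatives are described as matched 1:2 and similar to the positives, but Table 1 shows otherwise, and the background prevalence comparison has no stated adjustment

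*Protocol article*

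**What the plan says.** Section 2.2 says that negatives were "randomly selected in each strata with a distribution that matched (1:2) positives", with strata formed from age, sex, year-quarter of the test and municipality. The overall target was "A reasonable sample of ~20,000 negatives were additionally included (ratio 2:1"). The result claimed is "This procedure allowed to include a group of negatives, similar to the positives regarding sociodemographic and timing of testing". The Abstract (Methods) repeats this, calling the negatives "comparable in distribution of age, sex, municipality of residence and year-quarter of testing". Section 3.1 lists it as a strength: "Matching test-negatives to test-positives on key characteristics (i.e., sex, age, and year-quarter of testing) when sampling limits possible confounding".

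On analysis, section 2.7 says: "Prevalence of reported symptoms in post-COVID-19 condition participants will be compared to the prevalence in PCR negatives". No adjustment or standardisation is attached to that comparison. The same section separately plans multivariable models of positives against negatives and names age, sex and year-quarter among the possible confounders. Section 3.1 offers one weighting example for over- and under-represented subgroups: "by weighing these subgroups according to the distribution in the invited population".

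**The concern.** Sampling one negative for every two positives in every stratum forces the two groups to share the same age, sex and quarter distributions, apart from rounding. Table 1 prints those distributions, and they differ, most of all for the timing of the test.

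The first study question asks for the prevalence of post-COVID-19 condition, accounting for symptoms in people who tested negative. If the negatives are taken as balanced by design, a crude subtraction looks safe. If they are not balanced, the net prevalence mixes the effect of infection with differences in age, sex and time since test. The article itself treats two of these as relevant: the Introduction names female sex as an established risk factor, and 3.1.1 says recall bias arises mainly in people tested long ago.

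**Working it through.** **Inputs.** All counts are from Table 1 (section 2.2). The totals also appear in 2.3: "Invited for participation were 41,780 PCR COVID-19 positives and 19,875 negatives from test records registered in the registry".

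**Overall ratio.** 41,780 / 19,875 = 2.10 positives per negative, and 19,875 / 61,655 = 32.2%, as printed. Exact 1:2 sampling would need 41,780 / 2 = 20,890 negatives. The overall ratio is therefore roughly as stated.

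**Ratio by level.** Under 1:2 sampling, expected negatives = positives / 2.

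| Level | Negatives | Positives | Expected at 1:2 | Difference | Negatives per positive |
|---|---|---|---|---|---|
| Q2 2020 | 361 | 49 | 24.5 | +336.5 | 7.4 |
| Q3 2020 | 2,267 | 716 | 358 | +1,909 | 3.2 |
| Q4 2020 | 5,718 | 12,060 | 6,030 | -312 | 0.47 |
| Q2 2021 | 3,635 | 9,561 | 4,780.5 | -1,145.5 | 0.38 |
| Q4 2021 | 1,156 | 3,947 | 1,973.5 | -817.5 | 0.29 |
| Age 18–20 | 1,211 | 3,519 | 1,759.5 | -548.5 | 0.34 |
| Age 60–70 | 3,098 | 4,697 | 2,348.5 | +749.5 | 0.66 |
| Women | 9,958 | 22,986 | 11,493 | -1,535 | 0.43 |

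None of the 17 sex, age and quarter levels is within 3% of positives / 2. Allowing a constant ratio of 2.10 instead, three levels fit to within about 1.4% (ages 30–40 and 50–60, and Q4 2020), but the large gaps remain. For example, Q3 2020 would have about 341 negatives, not 2,267.

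**Shares, negatives against positives.**
- June–September 2020: (361 + 2,267) / 19,875 = 13.2%, against (49 + 716) / 41,780 = 1.8%.
- Age 60 or over: 5,074 / 19,875 = 25.5%, against 7,695 / 41,780 = 18.4%.
- Women: 50.1% against 55.0%.
- Standardised differences: year-quarter 0.46, age 0.20, sex 0.10.

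**Ordinary explanations.** Rounding adds at most one negative per cell, and a quarter has 8 × 2 × 16 = 256 cells, so at most 256. The excesses are 336.5 and 1,909. Using each person's last negative test would move negatives to later quarters, not earlier ones.

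**Possible effect on the crude difference (positive minus negative), with no effect of infection.** Shift = difference in share × assumed prevalence gap between levels. The document gives no prevalence by stratum, so gaps of 10 to 20 points are assumed, with higher prevalence in women, at 60 or over and in those tested early.
- Sex: (55.0% − 50.1%) × 10 to 20 points = +0.5 to +1.0 points.
- Age: (18.4% − 25.5%) × 10 to 20 points = −0.7 to −1.4 points.
- Quarter: (1.8% − 13.2%) × 10 to 20 points = −1.1 to −2.3 points.

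For scale, at an assumed prevalence of 30% the 95% confidence half-width is 1.96 × √(0.3 × 0.7 / n): 0.6 points for n = 19,875 and 1.4 points for an assumed 4,000 responding negatives.

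**Cost of standardising on quarter.** Weight = share of positives / share of negatives, from 0.06 (Q2 2020) to 1.62 (Q4 2021). Effective sample = 19,875 / Σ(positive share² / negative share) = 19,875 / 1.136, about 17,490, or 88%. Collapsing Q2 and Q3 2020 (2,628 negatives, 765 positives) gives a weight of 0.14 there and the same 88%.

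**The case against.** The strongest reply is that the planned models already list the three factors shown to be imbalanced. Section 2.7 presents the crude comparison only as some insight into background symptoms, and says its analyses are examples. An analysis plan that is not shown may standardise it. This stands, and it confines the point: the adjusted associations are not called into question.

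The size is also uncertain. The signs differ, so the shifts may partly cancel. The most imbalanced factor, test quarter, has the least obvious link to current symptoms, because everyone answered in one window (17 November 2021 to 9 January 2022). It bears more directly on symptoms recalled from the time of testing or dated from the test.

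A reader might infer three stronger claims that the document does not support:
- **That the weighting in 3.1 would keep the imbalance.** It would if each test group were weighted back to its own invited mix. It would not if both were weighted to one common invited population. The text does not say which.
- **That municipality is imbalanced or wrongly left out of the models.** Table 1 shows no municipality data, and the list of possible confounders is open-ended.
- **That the sampling program was faulty.** Filling a fixed total of about 20,000 from strata with surplus negatives, after others ran short, could produce this pattern. The article does not say this happened. If it did, the sample is still not matched 1:2 within strata.

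**Conclusion.** The contradiction is firm and needs no assumptions: the article claims stratum matching, similarity and control of confounding, and its own table shows a sample without that balance. The discrepancy is large for quarter of testing and smaller for age and sex.

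The consequence is narrower. It falls on the prevalence comparison serving the first study question, for which no adjustment is stated. The bias cannot be computed from the document. On the assumed 10 to 20 point gaps it is about 0.5 to 2.3 points per factor in either direction, which is modest but of the same order as the sampling error of the negatives' prevalence under the assumptions shown.

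**What to change.** 1. In the Abstract, 2.2 and 3.1, correct the statements on matching and similarity, or explain how and why the draw departed from 1:2. Stop crediting the sampling with control of confounding.
2. For the net prevalence, standardise negatives to the positives' age, sex and year-quarter distribution by raking on the margins or by model-based standardisation, with Q2 and Q3 2020 collapsed. Full four-way cells are not advisable: 8 × 2 × 7 × 16 = 1,792 cells would hold about two negatives each if 4,000 responded. Alternatively, weight both groups to one common target.
3. In 3.1, state what the weighting target is and whether it is the same for both test groups.
4. Check how negatives were drawn before further controls are sampled, since 3.1.2 foresees supplemental ones.

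The cost is wording and a modest amount of analysis code, plus a somewhat wider confidence interval for the negatives. The 88% effective sample covers quarter weights only, at full invitee numbers; adding age and sex, or having fewer responders, will change it. Respondents who declined registry linkage can be standardised only on self-reported values.
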